### Data Management

Data acquisition, handling, and storage are under the direction of the senior programmer of the Data Coordinating Center at the University of Washington. An HTML form-based web application is in use for conducting subject assessments as an efficient method for managing data for this multi-center, national trial. Data will be housed in a secure, centralized database at the University of Washington. The system will automatically perform edit and logic checks to validate the data for quality and completeness as they are being entered. A quality control audit will be performed on a monthly basis and the results printed in an interim report. Staff at the data-coordinating center will monitor the compliance of each study hospital with the study procedures and data quality.

We will document the number and proportion of subjects eligible for and compliant with each follow-up. Careful efforts will be made to minimize missing data, though some will inevitably occur. Subjects who withdraw from the study will be tabulated with the reasons for the withdrawal. Subjects who die during the study (unrelated to study or procedure) will be tabulated also. If the proportion of subjects withdrawn is larger than the expected 15% at one month and additional 10% at one year from either arm, an analysis of the demographic and prognostic characteristics will be made between subjects who withdraw and those who remain in the study. For continuous variables, parametric or non-parametric analysis of variance will be used. For categorical variables, Chi-square or Fisher's exact test will be applied.

When individual items are missing from a scale, we will calculate the percent of missing items. If the missing items are less than 10%, we will impute values using the mean of the remaining items. If more than 10%, the scale score will be missing, and unavailable for analysis at that time point.

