For primary analyses, an "intention-to-treat" strategy will be employed, such that each subject is analyzed in the group to which he or she is randomized, regardless of actual compliance with the intended intervention. This strategy requires minimal assumptions and maintains the random allocation, although intervention effects may be "diluted" if cross over between procedures is high. We will stratify all analyses for site. Non-adherence and/or dropout complicate analysis of follow-up data. Consideration of missing data is essential to characterize the potential for selection bias through attrition. When appropriate, missing follow-up data for subjects who withdraw will be imputed.

The primary outcomes of Roland and pain measure will be assessed at the one-month time point. This allows adequate time for any intervention benefit to manifest, and is the final assessment prior to the opportunity to select further treatment (crossover). The primary analysis will test for the efficacy of vertebroplasty using a permutation test based on the randomization distribution. Such analysis allows formal inference relying solely on the random assignment of subjects for validity (i.e., makes no additional statistical assumptions). Confidence intervals for the magnitude of treatment effect will be obtained using linear regression with a treatment indicator as the predictor of interest and using dummy variables to stratify on site. We will perform a similar analysis using the 0–10 numerical pain rating scale at one month. Secondary analyses will describe the complete time profile for the Roland and the pain ratings through one year using methods appropriate for the analysis of repeated measures [16].

In addition to hypothesis tests based on the randomization scheme, we will conduct secondary analyses that adjust for important baseline characteristics, such as baseline pain severity, and functional status. We will conduct limited exploratory analyses to assess evidence for differential treatment response by subject subgroups by testing treatment-covariate interactions for factors that are specified *a priori *in a detailed analysis plan to be created prior to data analysis. We will also perform a subgroup analysis examining whether enrolling early or late in the study had an effect on outcome. This will help determine if a significant learning curve was present and, if so, the magnitude of the effect.

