### Sample Size

In unpublished pilot data on 88 patients, we found an 8.6 point average reduction on the Roland (standard deviation of 6.7) at 4 weeks following the vertebroplasty procedure. We originally planned to enroll 249 subjects but had to adjust our expectations to 166 subjects due to difficulty with enrolment. With at least 90% follow-up at one month, we expect to have 75 subjects in each arm (150 total) assessed. This sample size yields 95% power to detect a 4-point effect size, and maintains good power for a 3-point effect size (78% power).

We will use a 0–10 numerical pain rating scale to test the hypothesis that short and long-term pain relief is greater in the percutaneous vertebroplasty group than in the control group. In a pilot study, we found a mean reduction of 7.1 (2.7 SD) points on this pain rating scale in a group of patients who received vertebroplasty [24]. A sample size of 150 has greater than 95% power to detect an effect size of 1.75 and a greater than 80% power to detect a 1.25-point effect size.

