## Discussion

Although extensively utilized throughout North America for palliation of pain, vertebroplasty still has not undergone rigorous study. The study outlined above represents the first randomized, controlled study that can account for a placebo effect in the setting of vertebroplasty.

Waning enrolment caused the addition of foreign sites to the study to have the number of subjects needed for an acceptable sample. Approval was obtained from the State Department and the NIH and some foreign sites were initiated into the study and enrolment increased. We now anticipate enrolling a total of 100 subjects. Assuming a 90% follow up rate at one month, we maintain good power (80%) to detect group differences in Roland of 4.0 or more and 87% power for differences in pain of at least 1.75.

Results from this study should provide compelling evidence as to whether or not internal stabilization of non-healing, painful, osteoporotic vertebral compression fractures offers clinical benefit.

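### Power is computed at 90% one-month follow-up, but Data Management expects 15% withdrawal by one month; at that loss four stated powers fall by about 2 to 2.5 points

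*Protocol article*

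**What the plan says.** Three sections of the Protocol article give a rate for the same time point.

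- Sample Size, for a target of 166: "With at least 90% follow-up at one month, we expect to have 75 subjects in each arm (150 total) assessed". On 150 assessed it claims 95% power for a 4-point and 78% for a 3-point Roland difference, and more than 95% for 1.75 and more than 80% for 1.25 points on the pain scale.
- Discussion, where the expected enrolment becomes 100: "Assuming a 90% follow up rate at one month", it claims 80% power for 4.0 Roland points and 87% for 1.75 pain points.
- Data Management: "If the proportion of subjects withdrawn is larger than the expected 15% at one month and additional 10% at one year from either arm", the demographic and prognostic characteristics of withdrawn and remaining subjects will be compared.

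The Analysis section places both primary outcomes at one month, so this rate fixes the number of subjects in the primary analysis.

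**The concern.** A trial cannot plan on at least 90% of subjects being assessed at one month and also expect 15% to have withdrawn by then. The two figures sit in adjacent sections and nothing explains the difference.

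The stated powers depend on the 90%. Some have little or no margin: the 80% for 4 Roland points supports the reduced enrolment of 100, and the claim of more than 80% for 1.25 pain points is only just met at 150 assessed. If the rate in Data Management is the real expectation, the article overstates its power. If the rate in Sample Size is, Data Management misreports the expectation.

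**Working it through.** **Inputs**
- Standard deviations: 6.7 (Roland) and 2.7 (pain), both from pilot data in Sample Size. For pain: "we found a mean reduction of 7.1 (2.7 SD) points on this pain rating scale".
- Enrolment: 166 (Sample Size) and 100 (Discussion), allocated 1:1.
- One-month follow-up: 90% (Sample Size, Discussion), or at most 85% (Data Management, 15% withdrawn).
- Alpha: not given with the power figures. Two-sided 0.05 is assumed because it reproduces them. For 3 Roland points at 150 assessed, alpha 0.025 would give 69% and one-sided 0.05 would give 86%, against the stated 78%.
- Test: Analysis plans a permutation test. A two-sample comparison of means is used here as its stand-in for power.

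**Formula (normal approximation)**, with n per arm: power = Φ( d / (SD × √(2/n)) − 1.96 ). A noncentral t calculation was run as a cross-check.

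**Assessed numbers**
- 90% follow-up: 100 × 0.90 = 90 (45 per arm). 166 × 0.90 = 149.4, which the article takes as 150 (75 per arm).
- 15% loss: 100 × 0.85 = 85 (42.5 per arm). 166 × 0.85 = 141.1, taken as 141 (70.5 per arm).

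**Worked example, 4 Roland points, 100 enrolled**
- 45 per arm: standard error 6.7 × √(2/45) = 1.412; 4/1.412 = 2.832; 2.832 − 1.96 = 0.872; power 80.8%.
- 42.5 per arm: standard error 6.7 × √(2/42.5) = 1.453; 4/1.453 = 2.752; 2.752 − 1.96 = 0.792; power 78.6%.

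**All stated powers** (normal approximation, t-test in brackets)

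| Enrolled | Difference | Stated | At 90% follow-up | At 15% loss | Change (normal) |
|---|---|---|---|---|---|
| 100 | Roland 4 | 80% | 80.8% (80.0%) | 78.6% (77.6%) | −2.2 |
| 100 | Pain 1.75 | 87% | 86.8% (86.0%) | 84.8% (84.0%) | −2.0 |
| 166 | Roland 3 | 78% | 78.3% (77.8%) | 75.8% (75.2%) | −2.5 |
| 166 | Pain 1.25 | >80% | 80.9% (80.4%) | 78.5% (77.9%) | −2.4 |
| 166 | Roland 4 | 95% | 95.5% (95.3%) | 94.4% (94.1%) | −1.2 |
| 166 | Pain 1.75 | >95% | 97.8% (97.6%) | 97.1% (96.9%) | −0.7 |

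Changes are taken before rounding. The stated figures are reproduced at 90% follow-up, with one dependence on method: 87% for pain 1.75 is reached only by the normal approximation (86.8%), while the t-test gives 86.0%. Setting the stated 87% against the t-test's 84.0% would therefore count about one point of method difference as attrition, so the change column stays within one method.

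**Enrolment that keeps the assessed numbers at 15% loss:** 90/0.85 = 105.9, so 106; 150/0.85 = 176.5, so 177.

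**The case against.** **The powers are right as stated.** Each is made explicitly conditional on 90% follow-up and is reproduced under that condition. This stands. A reader might infer that the powers were miscalculated, and the article does not support that. The defect is an inconsistent planning input.

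**The 15% is only a trigger, applied per arm.** With 10% lost overall, one arm can reach 15%, so a threshold need not equal the pooled allowance. That would answer the point if the text gave 15% only as a threshold. It calls 15% the expected rate, and applying it per arm does not lower the expectation.

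**The effect is small.** This stands. Raising the Roland SD from 6.7 to 6.9 at 90 assessed has much the same effect: 4/(6.9 × √(2/45)) − 1.96 = 0.790, or about 78.5%. The SD comes from a pilot of 88 patients, so it is uncertain by at least that much. The rows for 166 are also secondary, since the Discussion now anticipates 100.

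**Imputation covers it.** Analysis allows missing follow-up data to be imputed when appropriate. That does not reconcile the two rates.

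**Dropout is examined anyway.** A reader might infer that loss of up to 15% in an arm would go unexamined. That is too strong. Data Management always documents compliance with each follow-up and tabulates withdrawals with reasons, and Analysis treats missing data as essential to consider. Only the comparison of demographic and prognostic characteristics waits on the threshold, and a pre-specified threshold is not in itself an error.

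**Conclusion.** The inconsistency is real and concerns the primary time point: 90% followed up and 15% withdrawn cannot both be the expectation. At the 15% loss, four stated powers are missed. Those for the current enrolment of 100 become about 79% (t-test 78%) against 80%, and about 85% (84%) against 87%. For 166, the 78% becomes about 76% (75%), and the claim of more than 80% no longer holds, at about 78.5% (78%). The claim of more than 95% for pain 1.75 survives, and 4 Roland points slips to about 94% against 95%.

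Like for like, the four missed powers lose about 2 to 2.5 points. That does not undermine the design, but the power statement is a figure readers rely on and correcting it is cheap. The result rests on two-sided 0.05, the pilot SDs, equal arms, and reading 15% withdrawn as at most 85% assessed.

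**What to change.** Use one one-month attrition rate in Sample Size, Data Management and Discussion.

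- If 15% is the expectation, restate the powers at 85 assessed of 100 and name the method: about 79% for 4 Roland points and 85% for 1.75 pain points by the normal approximation, or 78% and 84% by t-test. If the 166 figures are kept, restate them at 141 assessed. The alternative is to keep 90 assessed by enrolling 106, six more than now anticipated, which may be hard given the enrolment difficulty the article describes.
- If 10% is the expectation, change the one-month figure in Data Management to 10%.

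Either wording change costs a few lines of text; the first also means acknowledging about 2 points less power.

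Optionally, produce the baseline comparison of withdrawn and retained subjects by arm whatever the loss. This adds one routine table and is an improvement rather than the correction of an error.

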## Discussion

Although extensively utilized throughout North America for palliation of pain, vertebroplasty still has not undergone rigorous study. The study outlined above represents the first randomized, controlled study that can account for a placebo effect in the setting of vertebroplasty.

Waning enrolment caused the addition of foreign sites to the study to have the number of subjects needed for an acceptable sample. Approval was obtained from the State Department and the NIH and some foreign sites were initiated into the study and enrolment increased. We now anticipate enrolling a total of 100 subjects. Assuming a 90% follow up rate at one month, we maintain good power (80%) to detect group differences in Roland of 4.0 or more and 87% power for differences in pain of at least 1.75.

Results from this study should provide compelling evidence as to whether or not internal stabilization of non-healing, painful, osteoporotic vertebral compression fractures offers clinical benefit.

## Conclusion

Achieving the sample size of enrolled participants will be difficult especially as the eligibility criteria are so limiting and most potential vertebroplasty patients come from quite a distance and are not willing to return at one month and one year.
